## Abstract

Supplemental Digital Content is available in the text

## Introduction

1

According to the Health Insurance Statistical Yearbook (2012–2016)^[1–5]^ published by the National Health Insurance Corporation and the Health Insurance Review and Assessment Service for the past 5 years in Korea, lumbar disc herniation (LDH) diagnosed as “Other intervertebral disc disorders (M51.0)” is the fifth highest among musculoskeletal diseases that cause pain. Moreover, LDH was first for 5 consecutive years among patients hospitalized with musculoskeletal diseases. Furthermore, in 2016, the number of patients diagnosed with “Other intervertebral disc disorders (M51.0)” had increased by about 100,000 over the 5 years since 2012. Also, the estimated number of patients receiving Korean Medicine treatment due to other intervertebral disc disorders is considered to be higher than the statistical value of 25,256 because clinically, many patients complaining of back and/or leg pain tend to receive symptomatic treatments without definite diagnoses. Thus, LDH not only makes daily living difficult but also poses a considerable burden on the costs of public healthcare.

In many studies, conservative treatments for LDH have been reported to be effective.^[6,7]^ Among those treatments, acupuncture is in the spotlight to such an extent as to have been upgraded to the recommended level in medical care guidelines.^[8,9]^ Acupotomy, which involves both an acupuncture needle and a surgical scalpel, was developed in 1976 by [name] of China. As a modern acupuncture treatment, it has been used to treat patients with pain caused by various diseases and can be used to remove chronic lesions in soft tissue. Some studies done in the Republic of Korea have reported acupotomy to be clinically effective, especially for patients suffering from pain due to LDH.^[10–12]^ However, those studies have all been case studies, so more extensive, well-designed, randomized clinical trials (RCTs) are needed to ensure the effectiveness and safety of acupotomy for treating patients suffering from pain due to LDH.

According to a pilot study implemented by our study team, the reductions in the pain intensity and the disability in the acupotomy group were statistically significantly superior to those in the manual acupuncture group, and acupotomy treatment was found to be as safe as a manual acupuncture treatment. Based on those results, we have planned a large-scale RCT to confirm the effectiveness and safety of acupotomy treatment for patients with back and/or leg pain caused by LDH.

## Methods

2

### Objective

2.1

In this multicenter, randomized, controlled, assessor-blinded, clinical trial, we will evaluate the effectiveness and safety of acupotomy for treating back and/or leg pain in patients with LDH. The objectives of this clinical trial are twofold: to compare the pain intensity on the visual analog scale (VAS) in the acupotomy group with that in the manual acupuncture group at 4 weeks after randomization and to investigate adverse events (AE) that occur during the study.

### Study design

2.2

This study will be performed as a multicenter, 2-arm parallel design, stratified block (male vs female) randomized, assessor-blinded, controlled, clinical trial. The flowchart for this trial is shown in Fig. 1. This study will recruit 73 applicants per group, for a total of 146 applicants, who meet the inclusion and the exclusion criteria (Table 1).^[13]^ A total of 146 patients with LDH will be recruited from outpatients at the Daejeon University Dunsan Korean Medicine Hospital (DUDKMH) and the Daejeon University Cheonan Korean Medicine Hospital through advertisements posted on bulletin boards at subway stations, apartments, and hospitals and on subway cars, hospitals’ homepages, newspapers, etc. Recruitment commenced in March 2018, and the trial is expected to end in February 2019.

**Figure 1 F1:**
[figure not shown]
Study flow with outcome assessments.

**Table 1 T1:**
[figure not shown]
Inclusion and exclusion criteria.

All participants will receive a full explanation of this study's protocol and will be provided a written explanation and informed consent form. Those who have not had computed tomography (CT) or magnetic resonance imaging (MRI) examinations within the past 5 years, but are suspected to have LDH based on history taking or a physical examination, will receive a lumbar spine CT scan. Also, blood tests, such as those for blood clotting factors, liver function, inflammation-related enzymes, and whole blood cells, will be provided. Participants who are judged to be eligible according to criteria for this study will be randomly assigned in a 1:1 ratio to either the acupotomy group or the manual acupuncture group. The intervention will begin within 2 weeks of the screening visit. The subject will receive a total of 4 interventions over 2 weeks, followed by 2 follow-up visits, 1 each at 2 and 4 weeks after the last intervention.

### Sample size calculation

2.3

Based on the results of a pilot study and clinical significance, we assume that the mean difference (δ) between the changes in the VAS before and after treatment in each group is 15 and the standard deviation (σ) is 24.71. When a significance level of 5%, a power of 90%, and an assignment ratio of the groups of 1:1 are applied, the number of subjects in each group (n) is given by^[14]^ 

Also, for an expected dropout rate of 20%, according to 

at least 73 subjects per group are required, for a total of 146 subjects.

### Randomization and blinding

2.4

The randomization will be performed by using a random number table that is generated by using the statistical program SAS Version 9.4 (SAS Institute Inc, Cary, NC) and is kept secret by the statisticians who are independent of this study. Stratified block randomization, which uses gender as a stratification factor, will be performed so that the sex ratio, which is the factor affecting the treatment, will be balanced in the 2 groups.^[15]^

This study is designed so that assessors, data collectors, and statisticians are blinded to the group assignment of the participants. Researchers who do not perform the intervention and randomization will assess the subjects. The assessment items and the contents for the purpose of completing the case report form (CRF) will be simply discussed with minimal dialogue, but will be closely evaluated. Furthermore, the study will be conducted in such a manner that the researchers will not know what intervention the subject is receiving. However, in this study, the 2 interventions are so different that blinding the clinicians and the subjects will be impossible. Thus, the clinicians of acupotomy and those of manual acupuncture will be separated from each other, and each clinician will perform only 1 kind of intervention; this should prevent biases due to intentional intervention by the clinicians. Moreover, the intervention clinicians will not participate in any assessment.

### Intervention

2.5

#### Acupotomy

2.5.1

The patients in the acupotomy group will receive a total of 4 acupotomy treatments over 2 weeks (Fig. 2). The needle for acupotomy (DongBang Acupuncture Inc, Chungcheongnam-do, Republic of Korea) with a circumferential shape, a diameter of 0.75 mm, and a length of 80 mm will be used. Before intervention, the clinicians will check the level of the herniated lumbar disc that has been diagnosed via a lumbar spine CT or MRI scan. When the subject is in the prone position, 2 to 6 points of the inner core muscles, which are placed bilaterally 20 to 30 mm from the spinous process of the level of the herniated lumbar vertebral disc and the soft tissue, which feels stiff and hard, will be selected by the clinicians. After the lumbar region has been sterilized with cotton saturated with 78% alcohol, the clinicians will take 1 to 2 g of emla cream 5% (AstraZeneca Korea, lidocaine and prilocaine, each 25 mg per 1 g) and spread it thinly on those 2 to 6 points and their environs. Then, this region will be covered and sealed with plastic wrap to block air so that it will be anesthetized. Next, that region will be sterilized using a cotton pad soaked with a 10% povidone-iodine solution. At the selected points, the 2 to 6 needles for acupotomy will be inserted to a depth of 50 to 70 mm, manipulated so as to alleviate the induration through incision and exfoliation, and then pulled out immediately without retention.^[16]^ Finally, the treatment areas will be sterilized and dressed with gauze. The methods for preventing infection at the treatment site will be carefully explained to all patients in the acupotomy group. All acupotomy treatments will be performed by Korean Medicine doctors who have had acupotomy treatment experience for more than 2 years. (See Appendix 1, Supplemental Content, which illustrates the STRICTA, Standards for Reporting Interventions in Clinical Trials of Acupuncture)

**Figure 2 F2:**
[figure not shown]
Application of acupotomy: (A) acupotomy needle, (B) skin disinfection, (C) needle insertion, (D) needle manipulation, and (E) disinfection and dressing.

#### Manual acupuncture

2.5.2

The patients in the manual acupuncture group will receive a total of 4 manual acupuncture treatments over 2 weeks as a control group. In this trial, 0.25 × 40 mm disposable sterile stainless-steel needles (DongBang Acupuncture Inc, Chungcheongnam-do, Republic of Korea) will be used. First, with the subject in the prone position, the lumbar region will be sterilized using cotton saturated with 78% alcohol. The acupuncture treatment will be performed on the local GV3 (Yaoyangguan) point, the bilateral BL23 (Shenshu), BL24 (Qihaishu), BL25 (Dachangshu), and BL26 (Guanyuanshu) points, and the distant bilateral GB30 (Huantiao), BL40 (Weizhong), and BL60 (Kunlun) points. For inducing Deqi sensation, we will rotate the needles left and right 3 to 5 times and then keep the needles in place for 15 minutes.^[17]^ After the needle has been removed, the treatment area will be disinfected using cotton saturated with 78% alcohol. All manual acupuncture treatments will be performed by Korean Medicine doctors who have had manual acupuncture treatment experience for more than 2 years. For compensation, after the trial is completed, the subjects in the manual acupuncture group will receive a maximum of 2 sessions of acupotomy treatment, upon request.

#### Cointerventions

2.5.3

All subjects will be instructed not to receive any treatment for back and/or leg pain, except for the treatments we provide. During the period of participation in the clinical trial, they will receive rescue medication (i.e., acetaminophen, up to 3000 mg per day). They will be instructed to take the rescue medicine only when their back and/or leg pain is so severe that it is unbearable. At each visit, the clinical research coordinator (CRC) will accurately record on the CRF the total rescue medication dosage used by the subject since the last visit.

At the discretion of the researching physician, all subjects will be allowed to continue to take medications that they were taking before their participation in this study. The subjects will be instructed to report to the researcher at each visit any changes in the dosages of the medications that they have been taking or any new medications that they have taken since they began participating in this study. They will also be instructed not to take arbitrarily a drug that might affect the study's outcomes. If the subject does not follow the above instructions and if the principal investigator (PI) judges that those actions could significantly influence the study's outcomes, that subject will be dropped from this study.

### Outcome measures

2.6

Assessments will be conducted at baseline and at 2 weeks (2W), 4 weeks (4W), and 6 weeks (6W) after randomization. The assessments at baseline and 2W during the intervention period will be performed before the assigned intervention for that visit. The schedule for the assessments of the results is shown in Table 2.

**Table 2 T2:**
[figure not shown]
Schedule for the treatment and the outcome measurements.

The primary outcome is the mean change in the VAS score for back and/or leg pain at 4W compared with baseline. The baseline VAS score will be measured immediately before the first intervention. The subject will indicate the degree of back and/or leg pain on a straight line of 100 mm. On that line, the left endpoint, 0, is no pain, and the right endpoint, 100, is the maximum pain imaginable.^[18]^

The secondary outcomes include back and/or leg pain at other time points, the clinical relevance^[19–22]^, dysfunction of the lumbar spine, range of motion of the lumbar spine, quality of life, and global assessment.

The clinical relevance will be assessed by comparing the percentage of subjects who indicate an improvement of more than 15 mm on the VAS, which corresponds to the Minimal Clinically Important Difference (MCID), of more than 30%, and of more than 50% between the 2 groups. In 2008, a consensus statement was issued that recommended MCID values for chronic pain assessment tools (pain, dysfunction, psychological factors, quality of life, etc.). According to a study that investigated the clinical relevance of the VAS for chronic back pain, the MCID was found to be greater than 15 mm based on the VAS (0–100 mm). Thus, in this study, we compare the proportions of subjects who have a decrease in the VAS score of 15 mm in each of the 2 groups. According to the above recommendation, in assessments using the VAS or the NRS, reductions of more than 30% and 50% in the MCID in chronic pain research suggest moderate clinically important changes and substantial improvements, respectively. Therefore, the main assessment tool of this study will be the VAS, so we will use it according to the criteria of the above recommendations.

The dysfunction of the lumbar spine will be assessed by using the mean changes in the scores on the Korean version of the Roland Morris Disability Questionnaire (RMDQ)^[23–26]^ at 2W, 4W, and 6W compared with baseline. The RMDQ was designed to measure the physical dysfunction of patients with back pain. Twenty-four questionnaire items will be simply answered “Yes (1) / No” (0), and the questionnaire will be scored from 0 to 24. A higher score indicates a greater degree of dysfunction. This survey has 2 advantages: the respondents can quickly complete the survey and the survey is easy to apply.

The range of motion of the lumbar spine will be assessed by using the mean changes in the measured values on the Modified-Modified Schober Test (MMST)^[27,28]^ at 2W, 4W, and 6W compared with baseline. The MMST is a physical examination that assesses lumbar vertebrae mobility. With the subject standing straight, the end points 10 cm above and 5 cm below a straight line based on the point where the mid-line of the vertebrae and the connection-line of both Posterior Superior Iliac Spines meet will be marked. Then, the researching physician will let the subject bend his or her lower back forward to the maximum extent while still feeling no pain and will then measure the amount of change in the distance between the 2 points.

The quality of life will be assessed by using the mean changes in the scores on the Korean version of the EuroQol Five Dimensions questionnaire (EQ-5D)^[29,30]^ at 2W, 4W, and 6W compared with baseline. The EQ-5D is the most widely used tool for measuring quality of life. Hence, only the EQ-5D Index will be used in this study.

The global assessment will be done by using the Patient Global Impression of Change (PGIC)^[31]^ at 4W. The PGIC is a method for assessing the alleviation of the symptoms that the subjects have felt themselves before and after treatment. The subjects are able to choose from 7 categories of responses to how much the back and/or leg pain has been reduced compared with before their participation in this study.

### Adverse events

2.7

In this study, all undesirable medical findings in which symptoms were not observed until participation in this clinical study will be classified as AEs. The researchers will carry out an AE assessment at each visit based on vital signs, history taking, and other test results. In addition, the subjects will be instructed to report voluntarily any adverse situations to the researchers at every visit, and the researcher will confirm such reports through medical examination. All identified AEs will be recorded on the CRF, regardless of their association with acupotomy treatment or manual acupuncture treatment. The researchers will assess the severity of the AE and take appropriate action. If serious adverse events (SAEs) occur, such as a life-threatening event or disorder or any other medically important condition, the PI should decide whether or not the subject should be dropped from this study.

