The primary outcome variable is the mean changes in the score on the VAS at 4W compared with the baseline and will be analyzed using an analysis of covariance with the covariates being the VAS score at baseline and the fixed factor that in each treatment group. Secondary outcome variables will be analyzed in the same manner as the primary outcome variable. If the outcome variables are categorical data, they will be analyzed using the chi-square test or the Fisher exact test. If necessary, a paired *t* test or Wilcoxon signed-rank test will be used for the primary and the secondary outcome variables to analyze differences in measured values before and after treatment in each group, and a repeated measures analysis of variance will be performed to test the difference in the trend at each visit. The Dunnett procedure will be used for multiple comparisons.

If necessary, subgroup analyses of outcome variables, such as demographic variables measured at baseline (e.g., gender, age, duration of illness, treatment expectancy, etc.), whether or not rescue medicines were taken, the amounts of rescue medications taken, the hospital at which the subject was treated, etc., may be conducted. The safety assessments will primarily be performed by analyzing the frequency of adverse events and SAEs that the researchers suspect to be associated with treatment. The collected safety data will be appropriately summarized. All adverse events that occur will be listed with a detailed description. All SAEs will be recorded descriptively. Adverse events will be collected through patient symptom reports and researcher observations. The frequency of each adverse event associated or not associated with intervention will be recorded and analyzed using descriptive statistics. No interim analysis will be performed.

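### The adverse event definition in section 2.7 covers only symptoms absent before participation, so worsening of the back or leg pain that participants bring to the trial is not an adverse event as written

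*Protocol article*

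**What the plan says.** Section 2.7 (Adverse events) sets the classification rule: "all undesirable medical findings in which symptoms were not observed until participation in this clinical study will be classified as AEs". The same section provides for broad collection. AEs are assessed at every visit, "the subjects will be instructed to report voluntarily any adverse situations to the researchers at every visit", and "All identified AEs will be recorded on the CRF, regardless of their association with acupotomy treatment or manual acupuncture treatment".

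Section 2.8 (Statistical analysis) then says: "The safety assessments will primarily be performed by analyzing the frequency of adverse events and SAEs that the researchers suspect to be associated with treatment". It adds two statements that widen the reporting: "All adverse events that occur will be listed with a detailed description" and "The frequency of each adverse event associated or not associated with intervention will be recorded and analyzed using descriptive statistics".

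Section 2.1 (Objective) makes the investigation of AEs the second of two objectives, next to the VAS comparison at 4 weeks. The Discussion closes with the expectation that acupotomy will prove equal to manual acupuncture in safety.

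**The concern.** A definition normally covers both new findings and the worsening of existing ones. This one is tied to symptoms not seen before participation. The trial treats back and/or leg pain due to lumbar disc herniation, so the symptom most directly exposed to the intervention is one that participants already have. A patient whose back pain becomes clearly worse after a session has an undesirable finding, but not a symptom that first appeared during the trial.

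This harm is plausible here, and its frequency could differ by arm. Acupotomy uses a 0.75 mm needle inserted 50 to 70 mm and manipulated to cut and separate tissue. The comparator is a 0.25 × 40 mm needle. The Discussion itself describes insertion of the acupotomy needle as painful enough to require skin anaesthesia. If aggravation is not classified as an AE, an AE table showing similar counts in the two arms would not support a conclusion of equal safety on this point.

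**Working it through.** **1. The definition against the condition treated.** The rule in 2.7 needs a symptom that was not observed before participation. The title condition, the objective in 2.1 and the primary outcome in 2.6 all concern back and/or leg pain, and the Discussion lists it among the grounds for diagnosis. For a symptom present at entry, the rule's condition fails however severe the symptom later becomes.

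**2. Does other text bring worsening back in?** Sections 2.5.3, 2.6, 2.7, 2.8 and 2.9 contain no statement on worsening of a pre-existing symptom. The request that patients report any adverse situation widens what is heard, but classification still follows the definition. Recording on the CRF, listing and tabulation in 2.7 and 2.8 all apply to AEs. An event that never qualifies as an AE reaches none of them.

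**3. Do the efficacy data tally it as harm?**

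| Source | What it captures | Why it does not fill the gap |
|---|---|---|
| VAS and RMDQ (baseline, 2W, 4W, 6W) | Each patient's pain and disability | Analysed as mean change, so individual worsening is averaged with improvement |
| VAS responder rates | Improvement of more than 15 mm, 30% or 50% | Count improvement only |
| PGIC (4W) | Patient's overall impression | One time point, described in terms of pain reduction |
| Rescue acetaminophen | Amount used since the last visit | Appears in the analysis only as an optional subgroup variable |

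Timing adds to this. The 2W assessment precedes that visit's intervention, and the next is at 4W. A flare after a 2W session that settles before 4W may leave no mark on the VAS.

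**4. Does the attribution rule remove events?** No. Section 2.8 gives first place to events suspected to be treatment-related. But 2.7 records AEs whatever their suspected cause, and 2.8 lists all of them and tabulates both related and unrelated ones. Attribution decides which count is called primary. The gap comes from the definition alone.

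**5. Size.** The plan states no AE rate, safety margin or safety power, so there is no safety figure to reproduce. The denominator can be checked. With δ = 15, σ = 24.71, two-sided 5% and 90% power, n = 2 × [24.71 × (1.960 + 1.282) / 15]² = 57.03, rounded up to 58. Then 58 / (1 − 0.20) = 72.5, rounded up to 73 per arm and 146 in total, as stated. The point does not depend on this figure.

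With an **assumed** aggravation rate p, the expected number of patients per arm outside the definition is 73 × p:

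| Assumed p | 73 × p |
|---|---|
| 5% | 3.65 |
| 10% | 7.30 |
| 15% | 10.95 |
| 20% | 14.60 |

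The definition applies to both arms. If the rates were equal, the omission would understate AEs equally and leave the difference in aggravation at zero. If they differed, for example 15% against 5%, the unseen difference would be 10.95 − 3.65 = 7.30 patients. Neither case can be chosen from the documents.

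**The case against.** The strongest reply is that little is really lost. AE assessment at each visit uses vital signs, history and test results, and patients may report anything adverse. New leg pain in a patient who entered with back pain alone, a new neurological deficit, bleeding, infection or needle-site injury all meet the definition as it stands. Only worsening of the same symptom is in doubt, and pain is measured repeatedly on the VAS, so aggravation does enter the arm comparison. The article also condenses a fuller protocol, which may hold better operational wording. No efficacy figure is affected.

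Most of this is correct and limits the point. It does not remove it. The article does not leave the definition to another document: it states one, and that one leaves worsening out. Pain data summarised as means do not report how many patients were made worse.

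A reader might infer more than the text supports, in three ways:

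- **That the attribution rule leaves events uncounted.** It does not, for the reasons in step 4 of the working.
- **That unblinded treaters judge causality.** Section 2.4 does say that "the 2 interventions are so different that blinding the clinicians and the subjects will be impossible". It also blinds assessors and keeps treating clinicians out of every assessment, and 2.7 and 2.8 give the AE judgement to the researchers. The article does not say whether those who judge causality are blinded. Reports from unblinded patients remain a possible route of bias, but judgement by unblinded treaters is not shown.
- **That the safety comparison is biased towards acupotomy.** The definition covers both arms, and no rates are given from which to derive a direction.

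**Conclusion.** The point holds for the definition. As written, section 2.7 does not classify worsening of a pre-existing symptom as an AE, and the symptom most affected is the one the trial treats. Aggravated back or leg pain would be missing from the AE counts in both arms, which weakens the second objective and the expected conclusion on comparative safety. This rests on reading the sentence literally and on the absence of any text that modifies it.

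The size is unknown. The range of about 4 to 15 of 73 per arm is only an assumption of 5% to 20%, and it further supposes that sites apply the rule literally in every case.

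The definition matters more than the order of the safety tables because it governs what is recorded: events never classified as AEs may not be recoverable at analysis. Putting related events first is a lesser matter of emphasis.

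**What to change.** **Section 2.7, main change.** Define an AE as any undesirable finding that is new, or that worsens from baseline in severity or frequency, from participation onward. State explicitly that this includes aggravation of back or leg pain or of neurological symptoms. Instruct both hospitals to record such findings on the CRF. Keep the window open from participation, as now: starting it at the first intervention would drop events in the interval of up to 2 weeks after screening.

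**Section 2.8, lesser change.** Make the by-arm frequency of all AEs, whatever their suspected relationship, the lead safety summary, and present treatment-related AEs second. The data and tables are already planned. This changes emphasis and does not recover uncounted events.

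**Cost.** Revised wording and a site instruction, using the history taking already done at each visit. Reported AE counts will rise in both arms, and the report should explain why. Section 2.2 says recruitment began in March 2018. For participants enrolled before the change, visit records would have to be re-read for noted worsening, and this recovers only what was written down.
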